### Secondary questions

Will there be a *difference in the health perceptions, behaviours, intentions regarding behaviours, health literacy and knowledge of resources* in senior residents living in subsidised seniors’ housing after receiving the CHAP-EMS programme compared to their own baseline measurement, and compared to seniors in a building not receiving the programme?*Will there be a difference in health-seeking behaviour (eg, number of hospital emergency room visits and primary care visits)* by senior residents living in subsidised seniors’ housing compared to baseline, and compared to seniors in a building not receiving the programme?

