### Recruitment process

Recruitment of intervention building residents into the CHAP-EMS programme will be organised in a multifaceted way. Existing building-based wellness groups and Tenants’ Associations will identify leaders from among the residents of the buildings who can champion the CHAP-EMS programme. The programme will also be advertised to the target population using posters in the intervention buildings. Posters will be translated into other languages as needed by the population composition in the buildings chosen.

Participants in the control buildings will receive usual care and will not be recruited for any intervention. The only contact the researchers will have with the participants of the control buildings will be to obtain survey responses regarding their health perceptions and behaviours at the beginning and end of the study. They will not be informed of the CHAP-EMS programme occurring in the matched intervention building.

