### Research intervention

The intervention includes BP, diabetes and fall risk assessments, health education/promotion, targeted referral to appropriate in-house wellness sessions and community resources, identification and referral of high-risk patients to their family physician, as well as regular communication of participants’ health information to their physician. The sessions will be held weekly in a common area of the intervention apartment buildings and will be implemented by paramedics from the local paramedic service who have undergone a structured training programme (3–4 h of online, interactive training modules, including case studies and the observation of an intervention session led by another paramedic) to assure intervention fidelity.

Individual participants will voluntarily attend and will complete the informed consent process with a paramedic on their first visit (see online supplementary appendix B). Following consent, they will have their risk factors assessed and entered into a database, and they will be advised to make lifestyle changes (if applicable) with the help of available community resources and educational pamphlets. Participants with a moderate-to-high score on CANRISK will be asked to return for a fasting blood glucose capillary test, where the paramedic will guide the participant through pricking his or her own finger with a lancet and applying a drop of blood to a test strip to measure fasting blood sugar. CANRISK assessments will be repeated at 6-month intervals to assess change.

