### Primary and secondary outcome measures

The primary outcome of EMS call rate (number of calls for building made by residents aged 55 years or older per 100 residents aged 55 years or older in the subsidised seniors’ building) will be available for each building from the EMS administrative database. The primary outcomes of change in measured systolic and diastolic BP, and difference in 10-year diabetes risk (CANRISK score), will be available from the measurements entered by the paramedics into the study database. The secondary outcomes will be difference in health perceptions, behaviours, intentions regarding behaviours, health literacy and knowledge of resources, measured by interviewer-led survey preintervention and postintervention; and difference in health-seeking behaviour (eg, number of ED visits/population 55 years and older), which will be based on administrative databases.

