### Data analysis

We will use an intention-to-treat analysis and generalised estimating equations (GEE) assuming a Poisson distribution and an exchangeable correlation structure within a building to evaluate healthcare utilisation, BP and risk assessment scores, as well as to identify factors contributing to these outcomes. Rate of EMS calls will be analysed at the building-level only, using GEE. We will perform pairwise comparisons of outcomes for each month during the preintervention and intervention periods. We will identify trends in the outcomes during the preintervention and postintervention observation periods. Subgroup analysis by clusters (each building) and by location will be performed. The HABiT survey data will be summarised as a numerical score representing the participants’ perceptions and behaviours regarding CVD and diabetes, and analysed with GEEs. The intracluster correlation coefficient (ICC) will be computed to determine the effect of clustering (by the building the participants reside in) on the participants’ scores. Other outcomes will be analysed using descriptive statistics.

All analyses requiring health administrative data will be performed in a two-step process. First, CHAP-EMS data with identifiers will be securely transferred to ICES for health record linkage, as per the participant consent form. Once linked, the data set will be de-identified for subsequent analysis. All analyses will be performed using SPSS V.20. Statistical significance will be set at α=0.05 and adjusted using the Bonferroni method for secondary analyses. Results will be reported as rate ratios, 95% CIs and associated p values.

Twice a month, the CHAP-EMS data will be reviewed and analysed to assess for errors in data entry, and assure fidelity to the planned intervention (eg, monitor referral patterns by EMS personnel and proper use of the screening tools). This trial did not warrant formal externally managed data monitoring, or a formal committee, due to its minimal risks. Instead, interim analysis will be conducted on the process measures to evaluate intervention recruitment and implementation, and to provide regular reports to local stakeholders (eg, EMS, public health, local housing). Collaborative research agreements with local partners (eg, housing) specify that aggregate data will be shared with these local stakeholders. Individual data will not be released without written permission from the participant.

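### The between-arm comparison of healthcare use has two conflicting analysis populations: all residents aged 55 and over, and a consent-linked set that can be selected differently by arm

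*Protocol article*

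**What the plan says.** Secondary questions (Protocol article) asks whether ED and primary care visits differ "compared to baseline, and compared to seniors in a building not receiving the programme". Primary and secondary outcome measures gives the ED example as "number of ED visits/population 55 years and older", taken from administrative databases. Data analysis places healthcare utilisation under intention to treat.

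The same section then sets the data route: "All analyses requiring health administrative data will be performed in a two-step process". The first step is that "CHAP-EMS data with identifiers will be securely transferred to ICES for health record linkage, as per the participant consent form"; the linked file is then de-identified for analysis.

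On consent in intervention buildings, Research intervention says: "Individual participants will voluntarily attend and will complete the informed consent process with a paramedic on their first visit". On control buildings, Recruitment process says: "Participants in the control buildings will receive usual care and will not be recruited for any intervention". It adds: "The only contact the researchers will have with the participants of the control buildings will be to obtain survey responses", at the start and end of the study.

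Two further statements concern the HABiT survey, which is run in both arms. Data gathering procedures says its results come from consenting participants and will be linked at individual level to administrative databases. Control of bias says the surveys will be anonymous.

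**The concern.** Randomising buildings protects a comparison of everyone in the buildings, or of people selected in the same way in both arms. It does not protect a comparison of residents who came to a programme session with whichever control residents happen to be linkable. Attendance follows allocation and exists in one arm only, so a comparison built on it is not intention to treat, whatever its label. Attenders may be healthier and more motivated than their neighbours, or sicker and heavier users of care. Either could create or hide a difference in ED or primary care visits. The Discussion ties lower ED use to healthcare savings, so the result would carry weight although it is secondary.

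**Working it through.** The protocol states no figure on this point, so there is none to reproduce. The check is to set the statements side by side and then illustrate the possible size.

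**Who is in the analysis, by section**

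| Section | Population implied |
|---|---|
| Primary and secondary outcome measures | All residents aged 55 and over |
| Data analysis, first paragraph | As randomised (intention to treat) |
| Data analysis, linkage paragraph | People with identified CHAP-EMS data and consent |
| Research intervention | In intervention buildings, programme consent is given by voluntary attenders at their first session |
| Recruitment process | Control residents have no session; survey contact only |
| Data gathering procedures | Survey results from both arms linked to administrative databases |
| Control of bias | Surveys anonymous |

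**Routes into the linked file**

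1. Session consent can supply intervention residents only.
2. The survey could supply residents of both arms, but an anonymous survey cannot be linked by identifier. As written, this route both exists and is closed.
3. If the survey is in fact identifiable, controls can be linked through it. The intervention arm could still add session attenders, a source that the controls lack.
4. Under any of these routes, the linked people are consenters, not the whole population aged 55 and over in the outcome definition.

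**Illustration of size (assumed inputs)**

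Let p be the share of residents who attend and r the ratio of attenders' to non-attenders' use of care. Take linked attenders against all control residents, with no programme effect. Setting the non-attender rate to 1, attenders have rate r and all residents have rate p·r + (1 − p). The null rate ratio is therefore

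r / (p·r + 1 − p).

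The documents give neither p nor r. The pilot reports 79 attenders in one building but not the number of residents, so uptake cannot be derived.

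| p | r = 0.8 | r = 0.9 | r = 1.25 | r = 1.5 |
|---|---|---|---|---|
| 0.2 | 0.83 | 0.92 | 1.19 | 1.36 |
| 0.3 | 0.85 | 0.93 | 1.16 | 1.30 |
| 0.5 | 0.89 | 0.95 | 1.11 | 1.20 |

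For example, p = 0.2 and r = 0.8 give 0.8 / (0.16 + 0.8) = 0.83; p = 0.2 and r = 1.5 give 1.5 / (0.3 + 0.8) = 1.36. If all residents aged 55 and over are counted in both arms, this selection term is 1.00.

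For scale only: the Sample size section treats a 10% difference as operationally significant for EMS calls. It names no such margin for ED visits.

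**The case against.** The strongest reply is that the linkage paragraph cannot mean literally every administrative analysis. The EMS call rate also comes from an administrative database and is analysed only at building level, so the paragraph may describe just the privacy steps for individual linkage at ICES. The ED definition has a population denominator, and Data gathering procedures lists hospital ED and ICES databases; its restriction to consenting participants is attached to primary care charts. On that reading, whole-building ED counts are already intended. This stands as a plausible intention. It does not remove the conflict: the building-level-only statement is made for EMS calls alone, and no such exception is given for ED or primary care visits.

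A reader might infer that the comparison is definitely one of volunteers with non-comparable controls, or that controls cannot be linked at all. The documents do not support either. Survey results from both arms are said to be linked, survey notification is worded the same for both arms, and the preintervention survey comes before the programme starts. The anonymity statement contradicts that route but does not show which statement governs.

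Baseline data also help. Preintervention administrative data are planned, and a stable difference between attenders and non-attenders would show there. They would not deal with attendance prompted by a recent change in health.

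Finally, the details may sit in the consent form or the full protocol. The point does not depend on what is left out: it rests on statements in the article that disagree.

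**Conclusion.** The point holds as an internal contradiction with a real consequence. The article gives a whole-population definition and an intention-to-treat label for healthcare use, and a data route that, followed as written, yields a consent-selected set whose selection can differ by arm. The between-arm contrast for ED visits, primary care visits and other linked use is then open to bias in either direction.

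Its size is unknown. The range of about 0.83 to 1.36 assumes 20–50% attendance, use ratios of 0.8–1.5, attenders compared with all controls, and no baseline adjustment. It shows that the bias could matter, not that it will occur or in which direction; a reader should not take it as predicting a spurious reduction.

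Only secondary outcomes are affected. The primary EMS call rate is counted by building and does not pass through consent.

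**What to change.** - State one population for the between-arm analysis of ED and other healthcare use: all residents aged 55 and over in the study buildings, in both arms. Obtain de-identified or aggregate counts by building address.
- Analyse these counts at building level within matched pairs, with the preintervention rate as a covariate.
- Limit consent-based linkage and primary care chart data to descriptive or before-after analysis of attenders, labelled as such. Make no between-arm claim from them.
- Reword the linkage paragraph in Data analysis so that it names the analyses it covers.
- Reconcile the statement that surveys are anonymous (Control of bias) with their individual linkage (Data gathering procedures).

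The cost is a revised data request and protocol wording. It assumes that the data holders can supply counts by building address, which the article does not say. Address-based counts will also misclassify some people who move in or out.

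### The secondary analyses use single-step Bonferroni; Holm's step-down procedure holds the same 0.05 family-wise error and can only gain power (optional improvement)

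*Protocol article*

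**What the plan says.** The Data analysis section of the protocol article sets the level and the multiplicity rule in one sentence: "Statistical significance will be set at α=0.05 and adjusted using the Bonferroni method for secondary analyses". The next sentence says that results will be given as rate ratios with 95% CIs and p values; it does not mention intervals adjusted for multiplicity.

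The number of tests in the secondary family is not stated, and the text can be read in several ways:

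- Primary and secondary outcome measures lists, for the survey, "difference in health perceptions, behaviours, intentions regarding behaviours, health literacy and knowledge of resources", which is five constructs. It adds health-seeking behaviour, with ED visits as an example.
- Secondary questions also gives primary care visits as an example. It asks for health-seeking behaviour to be "compared to baseline, and compared to seniors in a building not receiving the programme", and asks for the same two contrasts for the survey.
- Data analysis points to a shorter family: "The HABiT survey data will be summarised as a numerical score representing the participants’ perceptions and behaviours regarding CVD and diabetes". It leaves outcomes not otherwise mentioned to descriptive statistics.

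The Sample size section sizes the trial on EMS calls alone. No power is claimed for any secondary outcome.

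**The concern.** Single-step Bonferroni compares every p value with 0.05/m. Holm applies that threshold to the smallest p value only, then relaxes it step by step: 0.05/(m-1), 0.05/(m-2), and so on, stopping at the first failure. The error guarantee is the same and needs no extra assumption about dependence. As a testing rule, Bonferroni therefore has no advantage to set against its lower power.

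The secondary outcomes carry weight in this trial. Under Primary questions, BP and CANRISK are compared only with participants' own baseline, and EMS calls are analysed only at building level. The secondary outcomes are therefore the individual-level measures with a comparison against control residents. The Discussion expects one programme to change both health behaviour and ED visits, so several real effects at once is a case that the authors themselves have in mind. In that case some effects that Holm would declare may be reported as not significant.

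**Working it through.** **Inputs from the article.** Overall level 0.05 and Bonferroni for secondary analyses (Data analysis).

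**Assumptions.** Tests are two-sided z tests. Each real effect has 80% power at an unadjusted 0.05. Correlation between tests is 0 or 0.5. The family size m is varied because the article does not give it: m = 2 or 3 if the survey is one score, 7 if five constructs and two utilisation measures are tested separately, and 14 if each of those 7 is tested against baseline and against control.

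**Step 1: the plan's own figure.** The sum of the thresholds is m × 0.05/m = 0.05, which bounds the family-wise error for any m and any dependence. With independent tests the exact value is 1 - (1 - 0.05/m)^m, which is 0.0494 for m = 2 and 0.0490 for m = 6. The stated 0.05 is met.

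**Step 2: Bonferroni power.** The non-centrality is 1.960 + 0.842 = 2.802. Power per real effect is Φ(2.802 - z), where z is the two-sided critical value at 0.05/m.

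| m | threshold | z | power |
|---|---|---|---|
| 2 | 0.0250 | 2.241 | Φ(0.560) = 71.2% |
| 3 | 0.0167 | 2.394 | Φ(0.408) = 65.8% |
| 7 | 0.0071 | 2.690 | Φ(0.111) = 54.4% |
| 14 | 0.0036 | 2.914 | Φ(-0.112) = 45.5% |

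**Step 3: Holm by hand for m = 2, independent tests.** A hypothesis is rejected if its p value is at most 0.025, or if it lies between 0.025 and 0.05 and the other p value is at most 0.025.

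- Both effects real: 0.712 + (0.800 - 0.712) × 0.712 = 0.775.
- One effect real: 0.712 + (0.800 - 0.712) × 0.025 = 0.714.

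The gain is about 6 points in the first case and 0.2 points in the second.

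**Step 4: larger families by simulation** (at least 100,000 replicates per setting; ranges cover correlation 0 to 0.5). Average power per real effect:

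| Real effects | Bonferroni | Holm |
|---|---|---|
| 1 of 2 | 71% | 71% |
| 2 of 2 | 71% | 76-77% |
| 3 of 3 | 66% | 74-75% |
| 3 of 7 | 54% | 57% |
| 7 of 7 | 54% | 65-66% |

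In the cases with some null effects, Holm's family-wise error was at most 0.046, and Holm never missed a rejection that Bonferroni made. The chance of detecting at least one real effect changes by at most 0.2 points, because both rules use the same first threshold. The gain is in the second and later findings.

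**The case against.** The strongest reply is that nothing is wrong. Bonferroni is prespecified, valid under any dependence and simple, and it conflicts with nothing else in the article. That stands: this is a choice between two valid methods, not a correction.

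Bonferroni also gives matching simultaneous intervals directly, each at level 1 - 0.05/m, and Holm has no simple equivalent. This is a real advantage. The article states only 95% CIs and does not say whether they are adjusted, so as written it does not claim the advantage. A fuller analysis plan might.

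A reader might go further in four ways that the article does not support:

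- *That real secondary effects will be missed.* No secondary effect size, power or number of tests is given, so only *may be missed* is supportable. The larger gains need most or all effects to be real.
- *That the family is long, so the loss must be large.* Data analysis describes the survey as one numerical score, which points to a short family. If, on the other hand, monthly comparisons and subgroup analyses count as secondary analyses, many hypotheses may be null, and Holm then gains little.
- *That correlated outcomes are where Holm gains most.* The gain depends on how many effects are real. Moving the correlation from 0 to 0.5 slightly reduces it.
- *That the family should be cut to between-arm comparisons at the same time.* Secondary questions also asks for comparisons with baseline. Removing them from the adjustment would loosen error control, which is a separate decision and is not argued for here.

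**Conclusion.** The point holds as a small, free improvement of optional grade. Under the assumed 80% unadjusted power, Holm raises average power by about 5 to 6 points with 2 of 2 effects real, 8 to 9 points with 3 of 3, 2 to 3 points with 3 of 7, and 10 to 12 points only if all 7 are real. With one real effect there is essentially no gain. These sizes rest on assumed power and family sizes that the article does not supply. The ranking does not: Holm is never less powerful, whatever the family size, the correlation or the number of real effects. The family-wise limit of 0.05 is unchanged, and the primary outcomes are untouched.

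**What to change.** In the Data analysis section, or in the statistical analysis plan if the wording is carried there, replace the Bonferroni method with Holm's step-down procedure at a family-wise level of 0.05. Apply it to the same family of secondary analyses that the plan already adjusts; do not narrow or widen that family as part of this change.

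The cost is one sentence: no extra data, no extra tests and no added error risk. The one thing given up is simple simultaneous intervals that match the tests. If the investigators do intend to report multiplicity-adjusted intervals, keeping Bonferroni is reasonable, and a sentence saying so would settle the matter.

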**Methods/analysis:**

This is a pragmatic clustered randomised control trial in four communities across Ontario, Canada. Within each, four to eight seniors’ apartment buildings will be paired and within each pair one building will be randomly assigned to receive the Community Health Assessment Programme through EMS (CHAP-EMS) intervention, while the other building receives no intervention. During the 1-year intervention, paramedics will run weekly sessions in a common area of the building, assessing risk factors for cardiovascular disease, diabetes and falls; providing health education and referrals to community programmes; and communicating results to the participant's primary physician. The primary outcomes are rate of emergency calls per 100 residents, change in blood pressure and change in Canadian Diabetes Risk (CANRISK) score, as collected by the local EMS and study databases. The secondary outcomes are change in health behaviours, measured using a preintervention and postintervention survey and healthcare utilisation, available through administrative databases. Analysis will mainly consist of descriptive statistics and generalised estimating equations, including subgroup cluster analysis.

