### Primary questions

Will there be a *difference in the rate of EMS calls* in subsidised seniors’ housing buildings receiving the CHAP-EMS programmes compared to buildings not receiving the programme?Will there be a *change in measured systolic and diastolic BP* in senior residents living in subsidised seniors’ housing after receiving the CHAP-EMS programme compared to their own baseline measurement?Will there be a *difference in 10-year diabetes risk, as measured using the CANRISK tool,* in senior residents living in subsidised seniors’ housing after receiving the CHAP-EMS programme (healthy lifestyle education) compared to their own baseline measurement?

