The primary outcome (rates of EMS calls) and secondary outcomes will be analysed at the beginning of the intervention (preintervention data), and after the 12-month intervention period (postintervention data and full data analysis).

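### The protocol names three primary outcomes in three places and only one in another, so it is unclear whether blood pressure and CANRISK are tested at an unadjusted 0.05 or under Bonferroni

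*Protocol article*

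**What the plan says.** Three places in the protocol article give several primary outcomes.

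- Abstract, Methods/analysis: "The primary outcomes are rate of emergency calls per 100 residents, change in blood pressure and change in Canadian Diabetes Risk (CANRISK) score".
- Primary questions: the first asks about EMS calls "in subsidised seniors’ housing buildings receiving the CHAP-EMS programmes compared to buildings not receiving the programme". The second asks about "change in measured systolic and diastolic BP" and the third about "difference in 10-year diabetes risk, as measured using the CANRISK tool", each against the participants' own baseline.
- Primary and secondary outcome measures: the EMS call rate, systolic and diastolic pressure and CANRISK are all labelled primary. The secondary outcomes listed are the survey measures and health-seeking behaviour.

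One place gives a single primary outcome. The last paragraph of Data analysis reads "The primary outcome (rates of EMS calls) and secondary outcomes will be analysed", and goes on to fix the times of analysis before and after the 12-month intervention.

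The error-control rule is also in Data analysis: alpha is 0.05 and is "adjusted using the Bonferroni method for secondary analyses". The article states no order of testing, no division of alpha and no rule for combining the primary results. The Sample size section applies the full 0.05 to the EMS call rate.

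**The concern.** The Bonferroni rule depends on whether an analysis is secondary, so the label of an outcome sets its significance threshold. The article gives blood pressure and CANRISK two labels, so their threshold is undetermined.

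Suppose the systolic comparison gives p = 0.03. If blood pressure is primary, that is a significant primary result at 0.05. If it is secondary, it fails under any Bonferroni family of two or more tests, since 0.05/2 = 0.025. The choice could be made after the data are seen, and either choice could cite the published protocol.

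If the three-outcome version governs, the trial could show no difference in EMS calls, the only outcome with a sample-size calculation and the only primary question that compares randomised buildings. It could still report a significant primary outcome from one of several unadjusted tests.

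**Working it through.** **Inputs**

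- Alpha 0.05, with adjustment for secondary analyses only (Data analysis).
- Number of primary tests: three if blood pressure counts as one outcome, as in the Abstract. Four if systolic and diastolic pressure are tested separately, as the Primary questions and outcome section suggest.
- Correlation between the systolic and diastolic tests: not given. Assumed range 0.3 to 0.8.
- Dependence between the EMS, blood pressure and CANRISK tests: not given. Assumed independent.

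The article gives no familywise error figure, so there is none to reproduce.

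**Reading A: three outcomes are primary.** With every null hypothesis true and k independent tests at 0.05, the chance of at least one false positive is 1 − 0.95^k.

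- k = 3: 1 − 0.95³ = 1 − 0.8574 = 0.143 (upper bound 3 × 0.05 = 0.15).
- k = 4: 1 − 0.95⁴ = 1 − 0.8145 = 0.185 (upper bound 4 × 0.05 = 0.20).

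Simulation of four two-sided tests, with only the two blood pressure tests correlated:

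| Systolic–diastolic correlation (assumed) | At least one false positive |
|---|---|
| 0 | 0.185 |
| 0.3 | 0.183 |
| 0.6 | 0.177 |
| 0.7 | 0.173 |
| 0.8 | 0.168 |

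As this correlation approaches 1, the figure falls to the three-test value of 0.143. Correlation between the two pressures alone therefore does not bring it near 0.05.

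**Reading B: the EMS call rate alone is primary.** There is one primary test at 0.05, so the primary error rate is 0.05. Blood pressure and CANRISK fall under Bonferroni.

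**What it would cost to keep several primaries under Bonferroni.** The threshold is 0.05/4 = 0.0125 for four tests (familywise error 1 − 0.9875⁴ = 0.049) or 0.05/3 = 0.0167 for three. Take a test designed for 80% power at two-sided 0.05 (two-sided is assumed, as the article does not state sidedness):

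- Power at 0.0125: Φ(1.960 + 0.842 − 2.498) = Φ(0.304) = 0.62. Sample size to restore 80%: (2.498 + 0.842)² / (1.960 + 0.842)² = 1.42 times.
- Power at 0.0167: Φ(1.960 + 0.842 − 2.394) = Φ(0.408) = 0.66. Sample size to restore 80%: (2.394 + 0.842)² / (1.960 + 0.842)² = 1.33 times.

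These ratios do not depend on the sample size stated in the article, which is not examined here.

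**The case against.** **The two readings exclude each other.** If the last paragraph of Data analysis governs, there is no inflation across primary outcomes. This stands. The 14% to 18.5% is conditional on Reading A, and testing each primary outcome at 0.05 is the plain reading of the alpha sentence, not something it says outright.

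**The single-primary sentence concerns timing and may be shorthand.** That is possible, but it does not remove the problem. If it is shorthand, Reading A governs and the primary tests are unadjusted. If it is meant literally, the Abstract, the primary questions and the outcome section carry the wrong label.

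**Three different questions need not share one error rate.** Whether they should is debated, and an all-must-succeed rule would need no adjustment. The article states neither position.

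**The analysis plan may settle it.** Detail may be left there. But the article itself fixes alpha, the scope of the adjustment and two conflicting sets of labels, so this is a contradiction in what is stated.

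Three stronger readings are tempting, and the document does not support them.

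- A reader might infer a further route to success from "We will perform pairwise comparisons of outcomes for each month during the preintervention and intervention periods". Nothing in the text gives these monthly comparisons a role in declaring success or places them outside the secondary analyses that Bonferroni covers.
- A reader might count the Sample size section, which treats call rates as the main outcome, as a second contradiction. One outcome can be foremost among several primaries, so that wording fits either reading.
- A reader might expect a multiplicity correction to remedy the own-baseline design of the blood pressure and CANRISK questions. Bias in an uncontrolled before-after comparison is a separate matter, which a stricter threshold neither measures nor cures.

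**Conclusion.** The protocol contradicts itself on which outcomes are primary, and the contradiction determines whether blood pressure and CANRISK face 0.05 or a Bonferroni-adjusted level. That inconsistency is certain from the text.

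The size is conditional. If the three-outcome labels govern, the chance of at least one false-positive primary result is about 14% with three tests and 18.5% with four independent tests. It is 16.8% to 18.3% for four tests with an assumed systolic–diastolic correlation of 0.3 to 0.8. These figures assume that all null hypotheses are true, that each test holds its nominal 5%, and that the three outcomes are mutually independent. Positive dependence among them would lower the figures. If the single-primary sentence governs, the primary error rate is 5%. It would be wrong to say that the plan definitely inflates its error to 18.5%, because the text does not settle which reading applies.

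This should be corrected. It is a matter of wording and calls for no change to the conduct of the trial.

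**What to change.** Name the 12-month EMS call rate, intervention versus control buildings, as the sole primary outcome tested at 0.05. Say so in the same terms in the Abstract, the research questions, the outcome section and Data analysis. This agrees with the last paragraph of Data analysis and with the only sample-size calculation. List systolic pressure, diastolic pressure and CANRISK as secondary, and state that they count in the family to which the existing Bonferroni rule applies.

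The cost is an edit, ethics board review and a registry update, a route that the Ethics and dissemination section already provides for. No more participants are needed. The price is stricter thresholds for blood pressure and CANRISK, and two of the three primary questions become secondary.

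If the sponsor wants to keep all three as primary, an explicit rule would also resolve the point: a fixed testing order starting with EMS calls, an alpha split, or a requirement that all succeed. An equal Bonferroni split is costly: power for a test planned at 80% falls to about 62% with four tests or 66% with three, unless the sample grows by 1.42 or 1.33 times.
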